#### Statistical analysis

2.2.2

The *Kolmogorov–Smirnov* test of normality was used for all continuous variables in the 3 groups, and if *mean* *±* *SD* were used, the 3 groups had to be normally distributed. Comparisons between groups were made using *MANOVA*. Posthoc tests were undertaken using the *SNK* method and within-group comparisons were conducted using the *paired samples t test*. If the data did not conform to a normal distribution, comparisons between groups were made using a nonparametric test for paired samples, and comparisons between groups were made using a nonparametric test for multiple samples. Data is represented as *median (interquartile range)*. For discontinuous variables, examples (%) were used and the significance level was set at *P* < .05.

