## Method/design

2

The study was an assessor-blind, single-center randomized controlled trial. The aim of this study is to investigate the effect of SET combined with Long manipulation on pain, cervical function and muscle fatigue in patients with CRS. The project leader will be responsible for the overall project and will initiate the establishment of the subject project team. The subject project team will be responsible for subject security, recruitment and treatment and assessment, and quality control. The coordinating center staff will be responsible for communication of protocol changes and provision of information. The trial will have a 4-week period. After randomization, subjects will conduct assessments of primary and secondary indicators in 2 phases at 0 and 4 weeks (Fig. 1; Additional File 1).

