#### Exclusion criteria

2.1.2

1.Patients with serious chemical diseases.2.Patients with severe osteoporosis, anthropolising spondylitis, neoplasms, fractures and other pathologies.3.Those who do not collaborate with study.

Any potential subjects who meet the inclusion and exclusion criteria will be recruited from the outpatient and inpatient departments of the Department of Rehabilitation Medicine at Ningbo Haishu Rehabilitation Hospital. Potential subjects who meet the requirements will be interviewed by the research staff and informed of the inclusion criteria and procedures. Eligible subjects will first be analyzed through a baseline assessment and then diagnosed based on clinical presentation and physical examination, combined with imaging studies. Subjects will be informed that participation in the trial is strictly voluntary and that they can quit from the trial at any time. If you withdraw, the data collected will not be removed and will be used for the final statistical analysis. A summary table of data containing all variables and potential risks will be created by the research center. The raw information obtained will be stored in an electronic database for subsequent statistical analysis. Subject recruitment for the study will begin on December 31, 2021. A flow chart of the trial for subjects is shown in Figure 1.

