#### Sample size calculation

2.2.1

The study used G∗Power version 3.1 software for sample estimation and selected the F-test, which was calculated using the MANOVA model.^[17]^ Effect size = 0.30, α=0.05, power = 0.92, group size 3 and number of repeated measures of 2 were selected to generate a sample size of 81. Taking into account a possible attrition rate of 11% during the trial, the final sample size was obtained as 90 and was allocated in a ratio of 1:1:1, that is, 30 cases in each group.

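### The between-group analysis makes no use of the baseline values collected and does not say which MANOVA term compares the treatments; a week-4 ANCOVA adjusted for baseline would settle both at almost no cost

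*Protocol article*

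**What the plan says.** Under Statistical analysis (2.2.2) the protocol states "Comparisons between groups were made using" MANOVA, followed by SNK post hoc tests. Pre-post change appears only inside each arm: "within-group comparisons were conducted using the" paired t test. The section names no baseline covariate, no between-group change score, no time factor and no group-by-time term.

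Two other sections bear on what the MANOVA might be. Sample size calculation (2.2.1) uses a G*Power F-test, "which was calculated using the MANOVA model", with "Effect size = 0.30", α = 0.05, power 0.92, and "group size 3 and number of repeated measures of 2"; these inputs "were selected to generate a sample size of 81". Method/design says outcomes are assessed "in 2 phases at 0 and 4 weeks", and Table 1 shows VAS, NDI and the electromyography indices measured at both times. The first of the two measurements is therefore taken before treatment.

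**The concern.** Two things are unsatisfactory. First, a baseline value exists for every patient and every outcome, and the between-group comparison as stated ignores it. Where baseline and week-4 values are correlated, adjusting for baseline removes variance from the treatment comparison, and with 30 patients per arm that can matter.

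Second, the name MANOVA does not identify the test. With measurements at weeks 0 and 4 it could mean:

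- the group effect over both visits, which averages an untreated measurement into the treatment contrast;
- the group-by-time term, which with two visits is a comparison of change scores;
- a comparison at week 4 alone.

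These differ widely in power, and the reader cannot tell which one decides the trial. What is at stake is the chance of detecting a real difference and having one clear estimate of it, not the validity of the comparison.

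**Working it through.** **Inputs from the protocol.** Three arms, two measurements (weeks 0 and 4), f = 0.30, α = 0.05, stated power 0.92, N = 81 before attrition (Sample size calculation; Method/design).

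**Assumptions.** The protocol does not give the correlation ρ between baseline and week 4, so it is varied from 0 to 0.7. Arms are equal at baseline in expectation and the variance is the same at both visits. The 0.30 is taken as the effect at week 4; the protocol does not say which term it refers to. Figures are for one outcome at a time, using the overall F-test with noncentrality λ.

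**Step 1: reproduce the 81.**

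- Between-groups effect over two visits: λ = f²·N·2/(1+ρ), df 2 and N−3. At ρ = 0 and N = 81, λ = 0.09 × 81 × 2 = 14.58 and power is 0.928. The smallest N reaching 0.92 is 79, which becomes 81 with three equal arms.
- Univariate group-by-time interaction: λ = f²·N·2/(1−ρ), df 2 and N−3. At ρ = 0 this is also 14.58, so power is again 0.928 and N again 81.
- MANOVA interaction with f(V) = 0.30: N = 156. Global MANOVA on 1 to 10 outcomes: 30 to 57 (f² = 0.30) or 96 to 162 (f² = 0.09), and 81 did not appear.

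So 81 comes out equally from a main effect and from an interaction, both at an unstated ρ = 0. The sizing does not show which term will be tested.

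**Step 2: power at N = 81 for a week-4 effect of f = 0.30.**

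- Group effect over both visits: the effect becomes 0.15 and the variance of the mean is (1+ρ)/2, so λ = 0.15²·81/((1+ρ)/2).
- Change (group-by-time): λ = 0.30²·81/(2(1−ρ)).
- Week 4 alone: λ = 0.30²·81 = 7.29.
- ANCOVA: λ = 0.30²·81/(1−ρ²), with error df 77 instead of 78.

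At ρ = 0.5 the four values of λ are 0.0225 × 81/0.75 = 2.43; 0.09 × 81/1 = 7.29; 7.29; and 0.09 × 81/0.75 = 9.72.

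| ρ | Both visits averaged | Change | Week 4 alone | ANCOVA |
|---|---|---|---|---|
| 0 | 0.37 | 0.37 | 0.66 | 0.66 |
| 0.3 | 0.29 | 0.50 | 0.66 | 0.70 |
| 0.5 | 0.26 | 0.66 | 0.66 | 0.79 |
| 0.7 | 0.23 | 0.87 | 0.66 | 0.92 |

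Simulation (4,000 runs, 27 per arm) agrees. In the same column order it gives 0.267, 0.657, 0.655 and 0.779 at ρ = 0.5, and 0.230, 0.877, 0.662 and 0.923 at ρ = 0.7.

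**Step 3: precision and sample size.** The ANCOVA variance is (1+ρ)/2 of the change-score variance (75% at ρ = 0.5, 85% at 0.7) and 1−ρ² of the week-4-only variance (75% and 51%). At ρ = 0.5, 92% power needs 117 patients with ANCOVA, 156 with change or week 4 alone, and 456 with the averaged group effect.

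**Step 4: other effect sizes, at ρ = 0.5.** With f = 0.20, power is 0.33 for change or week 4 alone and 0.43 for ANCOVA. With f = 0.40 it is 0.90 and 0.96. The ordering does not change.

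**The case against.** The strongest reply is that the damaging reading is unproven. A reader might infer that the planned group effect averages in the untreated baseline, since the sizing uses two repeated measures and 81 can be reproduced that way. The documents do not support stating this as fact. The repeated measures appear only in the sizing text, the statistical section names no time factor, and the interaction reproduces 81 just as well. The non-parametric fallback, a test for several samples, also fits a week-4 comparison. This objection stands: the power of 0.23 to 0.37 is conditional on one reading.

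It is also fair that the gain depends on an unknown correlation. Over week 4 alone it is nil at ρ = 0 and about 4 points at 0.3. Over change it shrinks when ρ is high (0.971 against 0.983 at ρ = 0.8). And a condensed article may leave covariates and interval reporting to an analysis plan. That limits the point but does not remove it, because this article does name its between-group method and leaves the tested contrast ambiguous.

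A reader might add that MANOVA breaks the commitment for patients who withdraw, that "the data collected will not be removed and will be used for the final statistical analysis". That does not help the case for ANCOVA, which also leaves out a patient with no week-4 value, and the protocol does not say how such data will be used.

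**Conclusion.** The point holds as a recommendation on efficiency and clarity. The stated between-group method uses no baseline value and does not identify its treatment contrast. On the change and week-4-only readings the test is valid but no more powerful than baseline-adjusted ANCOVA. At ρ = 0.5 ANCOVA gains 13 points over both (0.79 against 0.66). At ρ = 0.7 it gains 5 points over change and 26 over week 4 alone. If the effect over both visits were the one tested, the loss would be large, but the protocol does not establish that it is.

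These sizes rest on N = 81, an assumed week-4 f of 0.30, equal variances at the two visits, and a correlation that the protocol does not give. A reader might take the finding as evidence of a biased or invalid analysis. It is not: randomisation protects the between-arm comparison whichever term is used.

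**What to change.** Replace the MANOVA sentence under Statistical analysis with wording to this effect: the week-4 value of each outcome is compared between arms by ANCOVA, with treatment as factor and the patient's own baseline value as covariate; adjusted mean differences with 95% confidence intervals are reported for combined versus Long manipulation, combined versus control, and Long manipulation versus control; and these pairwise contrasts are tested only after a significant overall F-test.

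That sequence controls the error rate across the three arms within one outcome. It does not control it across VAS, NDI and the electromyography indices, and the text should not claim that it does.

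The cost is one degree of freedom per outcome and a change of wording. No new data are needed, because the baseline assessments are already scheduled in Table 1.

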## Abstract

Neurogenic cervical spondylosis is the most common type of cervical spondylosis, accounting for approximately 60% percent of the incidence of cervical spondylosis. Cervical spine Long manipulation and sling exercise training (SET) have obtained good therapeutic results in clinical rehabilitation. The aim of this study was to evaluate the effect of Long manipulation combined with SET on neurogenic cervical spondylosis. In this assessor-blind, randomized controlled trial, 90 eligible patients will be randomized into a combination treatment group (Long manipulation combined with SET), a Long manipulation group and a conventional massage group. The visual analogue score, the Neck Disability Index score, and muscle fatigue in the bilateral upper oblique and Musculus sternocleidomastoideus, using mean power frequency and median frequency from the surface electromyography frequency domain index, will be assessed before and after the intervention at 0 and 4 weeks, respectively.

**Trial registration:** Registered in the Chinese Clinical Trial Registration Center with the number ChiCTR2100054978. Registered December 30, 2021.

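### SNK post-hoc testing gives no interval for combined minus Long, and its threshold for that pair shifts with the massage mean: a weakness in estimation, not in type I error

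*Protocol article*

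**What the plan says.** The Abstract frames the question as an effect: "The aim of this study was to evaluate the effect of Long manipulation combined with SET on neurogenic cervical spondylosis". Under Intervention (2.1.4) the combined arm receives the Long procedure unchanged plus sling training, so combined versus Long is the one comparison that isolates the sling component.

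Statistical analysis (2.2.2) then sets out the between-arm method:

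- **Overall test:** "Comparisons between groups were made using *MANOVA".
- **Pairs:** "Posthoc tests were undertaken using the *SNK* method".
- **Level:** "the significance level was set at *P* < .05".
- **If data are not normal:** "comparisons between groups were made using a nonparametric test for multiple samples", with medians and interquartile ranges. No pairwise follow-up is named on this path.

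On the normal path, arms are summarised as mean and SD. No pair is singled out as the main comparison, and the section mentions no between-arm difference or interval.

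**The concern.** SNK is a named choice of method, so this is more than a detail left to a fuller plan. It suits the stated aim poorly in two ways.

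First, it answers yes or no for each pair and has no standard matching confidence interval. A reader learns whether combined and Long fall in the same subset, but not how large the sling effect is or what sizes the data exclude.

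Second, the bar for that pair depends on the third arm. If the massage mean falls between the other two, the pair is judged as a range of three means. If massage is outermost, the pair is judged as a range of two, but only once the full range is significant. The same observed benefit of sling training can therefore be declared or not according to how the massage arm turned out.

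**Working it through.** **Inputs.** From Sample size calculation (2.2.1): "Effect size = 0.30, α=0.05, power = 0.92, group size 3 and number of repeated measures of 2 were selected to generate a sample size of 81", with "selected the F-test, which was calculated using the MANOVA model". Also "Taking into account a possible attrition rate of 11% during the trial, the final sample size was obtained as 90", allocated 1:1:1, so 30 per arm randomised and 81/3 = 27 per arm evaluable. Thresholds below are in SD units of a single outcome with equal variances.

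**The plan's own figure.** For a between-group F test with repeated measures, λ = f²·N·m/(1 + (m − 1)ρ), with df (2, N − 3). With f = 0.30, m = 2 and ρ = 0, power 0.92 needs N = 79, or 81 as a multiple of three. At N = 81, λ = 0.09 × 81 × 2 = 14.58 and power is 0.928. So 81 reproduces if the correlation was taken as zero; the article does not state it.

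**SNK threshold.** SNK compares (mean difference)/(s/√n) with the studentized range q, so the smallest significant difference is q/√n in SD units, and the equivalent t is q/√2.

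| Per arm | df | q for 2 means | q for 3 means | Adjacent | Massage between | Ratio |
|---|---|---|---|---|---|---|
| 27 | 78 | 2.815 (t 1.99) | 3.379 (t 2.39) | 0.542 SD | 0.650 SD | 1.20 |
| 30 | 87 | 2.811 (t 1.99) | 3.372 (t 2.38) | 0.513 SD | 0.616 SD | 1.20 |

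**One gap, three massage means** (30 per arm, observed combined minus Long = 0.58 SD, so pair q = 0.58 × √30 = 3.177):

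- Massage 0.30 SD above Long: range of three, 3.177 < 3.372, not significant.
- Massage 0.30 SD below Long: full range 0.88 × √30 = 4.820 > 3.372, then 3.177 > 2.811, significant.
- Massage 0.02 SD below Long: full range 0.60 × √30 = 3.286 < 3.372, so testing stops, not significant.

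**Simulated power for a true 0.6 SD sling effect** (27 per arm, 40,000 trials per setting):

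| Massage relative to Long (SD) | −0.6 | −0.3 | 0 | +0.3 | +0.6 |
|---|---|---|---|---|---|
| SNK | 0.584 | 0.566 | 0.500 | 0.450 | 0.498 |
| SNK after a significant overall F | 0.584 | 0.565 | 0.493 | 0.435 | 0.491 |
| Each pair at .05 after a significant overall F | 0.585 | 0.575 | 0.514 | 0.455 | 0.512 |

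A single combined-minus-Long contrast at .05 gives about 0.59 throughout. Tukey, which covers all three pairs with a fixed bar, gives about 0.43.

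**What an interval would show.** The 95% half-width is t × √(2/n): at 27 per arm, 1.991 × √(2/27) = 0.542 SD, or 0.650 SD with Tukey adjustment.

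**Combined-Long gap implied by f = 0.30.** This depends on the arm pattern, which the article does not give:

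- Equal spacing, combined and Long adjacent: 0.30 × √1.5 = 0.367 SD.
- Massage equal to Long: 0.30 × 3/√2 = 0.636 SD.
- Massage midway: 2 × 0.367 = 0.735 SD.

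**The case against.** **The trial can still state the effect.** A reader might infer that the trial will be unable to say how much sling training adds. The document does not support that. Means, SDs and arm sizes are to be available on the normal path, so the difference and an ordinary or Tukey interval follow directly, and nothing forbids reporting them. This stands: the limit belongs to SNK, not to the data.

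**SNK is valid here.** With exactly three arms it holds familywise error at 5% for each outcome. This stands too. The moving threshold is a property of a valid test, and the 0.59 for a single contrast is not a like-for-like rival because it does not cover all three pairs.

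**A gated alternative also moves.** Testing each pair only after a significant three-arm F test has the same dependence. With massage exactly midway, F = n·d²/4 must exceed 3.11, so d must exceed √(4 × 3.11/27) = 0.679 SD; with massage far away the bar is 0.542 SD. This is correct, and it limits what such a rule can be claimed to do.

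**The interval need not exceed the design effect.** A reader might set the 0.54 SD half-width against 0.37 SD and conclude that it always does. That holds only for the equally spaced pattern; 0.64 and 0.73 SD both exceed 0.54.

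**This is a condensed article.** Intervals and rank-based pairwise follow-up may sit in a full plan. That is fair for the non-normal path, where the sentence is also garbled. It does not remove the named choice of SNK.

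**Conclusion.** The point holds as one about estimation. The stated pairwise method gives no interval for the contrast that answers the sling question. Its bar for that contrast is 0.54 or 0.65 SD at 27 per arm, a 20% difference set by the massage mean, with the further condition on the full range when massage is outermost. Type I error per outcome is not in doubt, and the difference remains recoverable from the planned summaries.

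The figures assume 27 evaluable patients per arm, equal variances and one outcome at a time. The power figures also assume a true 0.6 SD effect, which is illustrative and not taken from the protocol. The change is worth making because it bears on the central comparison and costs almost nothing.

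**What to change.** In 2.2.2, replace SNK with planned pairwise mean differences and 95% CIs from the same model for each outcome. Name combined minus Long first as the key contrast, then combined minus massage and Long minus massage. If the rank path is used, give Hodges-Lehmann differences with 95% CIs for the same pairs.

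If familywise control over all three pairs is wanted, test each pair at .05 only when the univariate three-arm test for that same outcome is significant. In 200,000 simulations this kept the error at 0.049. The gate must not be a MANOVA across outcomes: a real effect on one outcome could then open it for a null outcome, where three unadjusted tests give a familywise error of about 0.12. Behind the same univariate test, this rule never rejects less often than SNK, because every SNK rejection already exceeds t = 1.99; the gain is up to about 2 percentage points. It does not remove dependence on the massage arm. Only pre-specifying the single combined-minus-Long contrast does that.

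The cost is one paragraph, with no added patients, visits or data.

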## Introduction

1

Research has confirmed that the degree of muscle fatigue is also associated to its stiffness, which is a manifestation of muscle tension and increases as muscle fatigue increases. The onset of cervical spondylosis is the result of a series of symptoms and signs caused by an imbalance between the cervical vertebrae and the adjacent soft tissues, and is the result of muscle fatigue caused by long-term tension in the neck and shoulder muscles.^[1]^ Due to degenerative changes in the cervical intervertebral discs, growth of the hook or synovial joints, and hypertrophic bone spurs protruding laterally, the nerve roots at the corresponding level are stimulated or compressed, and a series of diagnostic manifestations of nerve root irritation or dysfunction of the corresponding segment occur, characterized by pain in the back of the shoulder, radiating pain in the upper limbs and fingers, numbness and weakness, etc, which are more common unilaterally, and the prognosis is mostly good, but these clinical symptoms seriously affect people's quality of life.^[2]^

At present, there are many nondrug conservative treatment methods, such as acupuncture, massage, herbal compresses, low frequency therapy, and microwaves, all of which are effective. Numerous studies have shown that the clinical efficacy of conservative treatment and surgical treatment is the identical.^[3]^ Therefore, it is important to investigate how best combined conservative treatment can be used to improve neck pain and nerve root symptoms in patients with radiculopathy and to alleviate the progression of cervical spondylosis.

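### Within-arm before-after tests are planned at P < .05 without being marked descriptive, and the non-normal fallback calls a paired-sample test a between-group comparison

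*Protocol article*

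**What the plan says.** All references are to the protocol article.

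- **Statistical analysis, between arms.** "Comparisons between groups were made using" MANOVA. "Posthoc tests were undertaken using the" SNK method.
- **Statistical analysis, within arms.** "within-group comparisons were conducted using the" paired-samples t test. With assessments only at 0 and 4 weeks, this is a before-after test in each of the three arms.
- **Statistical analysis, non-normal data.** "comparisons between groups were made using a nonparametric test for paired samples". The same sentence then gives between-group comparisons a second time, now with a multiple-sample test. The within-group comparison is not named at all.
- **Statistical analysis, level.** "the significance level was set at" P < .05. This is stated once and generally. Sidedness is not given, and no test is called descriptive.
- **Sample size calculation.** The authors "selected the F-test, which was calculated using the MANOVA model", so the trial is sized on a three-group comparison and not on a paired test.
- **Introduction.** Of the symptoms of this condition, the article says that "the prognosis is mostly good".

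**The concern.** Randomisation protects comparisons between arms. It does not protect a before-after comparison inside one arm, which mixes any treatment effect with natural recovery, regression to the mean and expectation. Each of these is plausible here. Patients must be symptomatic to enter, only the assessors are blinded, pain is scored by the patient, and every arm receives active hands-on treatment, so no arm shows the untreated course.

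Two misreadings are then possible. If change is large, every arm reaches P < .05 and each treatment seems proven. If change is moderate, some arms reach P < .05 and others do not, which looks like a difference between treatments although none has been tested. The plan offers many occasions for this: VAS, NDI, and two frequency indices for two muscles on two sides make 2 + 2 × 2 × 2 = 10 variables, hence 10 × 3 = 30 within-arm tests.

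The fallback sentence adds to the risk. Taken literally, it presents a before-after test as a comparison between groups, which is the very distinction that has to be kept.

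**Working it through.** **1. The plan's own figure, and the arm size used.** The Sample size calculation gives effect size 0.30, α = 0.05, power 0.92, 3 groups, 2 measurements and N = 81. A repeated-measures between-factors F test has λ = f²·N·m / (1 + (m − 1)ρ). With ρ = 0 (the document states no correlation), λ = 0.09 × 81 × 2 / 1 = 14.58 on (2, 78) df, and power is 0.928. The minimum N for power 0.92 is 79, or 81 as a multiple of 3. The stated 81 therefore reproduces at ρ = 0. It gives 81 / 3 = 27 analysed per arm; recruitment is 30 per arm.

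**2. Inputs not in the documents (assumptions).** The true change is the same in all three arms, outcomes are normal, arms are independent, tests are two-sided at 0.05, and the week 0 to week 4 correlation is 0.5. The paired t test depends on dz = δ / √(2(1 − ρ)), where δ is the change in units of the outcome SD. At ρ = 0.5, √(2 × 0.5) = 1, so dz = δ.

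**3. Formulas.** Per-arm probability p of a significant paired t test: noncentral t with n − 1 df and noncentrality dz·√n. All three arms significant: p³. Arms disagree (at least one significant, at least one not): 1 − p³ − (1 − p)³.

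**4. Results, n = 27 per arm, no true difference between arms.**

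| Change (SD) | p per arm | All three significant | Arms disagree |
|---|---|---|---|
| 0.3 | 0.324 | 3% | 66% |
| 0.4 | 0.517 | 14% | 75% |
| 0.5 | 0.706 | 35% | 62% |
| 0.6 | 0.851 | 62% | 38% |
| 0.8 | 0.979 | 94% | 6% |

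Worked line at 0.5 SD: 0.706³ = 0.352; 0.294³ = 0.025; 1 − 0.352 − 0.025 = 0.623.

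With 30 per arm, disagreement is 69%, 74%, 56% and 3% at 0.3, 0.4, 0.5 and 0.8 SD. With no change at all it is 14% at either size.

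**5. Sensitivity to the correlation.** A change of 0.5 SD is dz = 0.5 / √2 = 0.35 at ρ = 0, and 0.5 / √0.6 = 0.65 at ρ = 0.7. At n = 27, disagreement then lies between 66% and 75% in the first case and between 6% and 38% in the second.

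**6. The between-arm test in the same setting.** In 20,000 simulated trials per setting, an F test comparing change scores across the three arms rejected in 4.6% to 5.1% of trials at changes of 0, 0.3, 0.5 and 0.8 (n = 27 and n = 30). This is a stand-in for the planned MANOVA. It shows that a direct comparison keeps its error rate where comparing separate P values does not.

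**The case against.** The strongest case against has five parts.

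- **The proper comparison is already planned.** MANOVA with SNK comes first in the section and the trial is sized on a MANOVA F test. This stands: the within-arm tests are additional and do not invalidate the between-arm test.
- **No misuse is announced.** A reader might infer that ordinary recovery will be presented as proof of efficacy or as a difference between arms. The documents do not support that: nowhere do they say that within-arm P values will carry efficacy claims or be compared across arms. Equally, nothing rules it out.
- **The Introduction's remark on prognosis proves little.** It gives no timescale and does not refer to untreated patients, so it does not establish that every arm would improve over 4 weeks without a treatment effect. It makes improvement plausible, no more.
- **The magnitudes depend on assumed changes.** This stands. Disagreement between arms is a problem of moderate change and falls to about 6% at 0.8 SD. The 94% at 0.8 SD is not a false-positive rate either: if every arm truly changes, rejecting no change is correct. The fault would lie in attributing the change to treatment.
- **The labelling may sit in a statistical analysis plan not shown, and baseline adjustment goes beyond a label.** An unseen plan does not undo an analysis that the article states, nor the error in the fallback sentence. Adjustment is indeed a change of model, and its cost should be counted as such.

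**Conclusion.** The point holds as a conditional one. The article plans non-randomised before-after tests at the same P < .05 as the randomised comparison, does not mark them as descriptive, and mislabels a paired-sample test in the fallback. If those P values are read as efficacy or set side by side across arms, they mislead often: with equal true change, 27 per arm and correlation 0.5, the arms disagree in 62% to 75% of trials at changes of 0.3 to 0.5 SD, and all three are significant in 94% at 0.8 SD. The sizes of change, the correlation, equal change in all arms and two-sided testing are assumptions; the arm size follows from the stated 81. It is not shown that the trial will draw false conclusions or that its between-group analysis is invalidated by the extra tests. The wording should be changed before analysis.

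**What to change.** In the Statistical analysis section:

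1. Replace the within-group paired t tests, and any paired nonparametric version, with within-arm mean change and 95% CI (median and interquartile range if non-normal), labelled descriptive and without P values.
2. State that efficacy conclusions rest only on the between-arm comparison, made on week-4 values adjusted for the baseline value.
3. Rewrite the fallback sentence so that a paired-sample test is not called a between-group comparison and only the multiple-sample test serves that purpose.

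Cost: a few sentences and a modest change of model. The Sample size calculation, now based on a MANOVA F test with two repeated measures, has to be aligned with the baseline-adjusted comparison. Baseline and week-4 values are already collected, so no new data are needed.

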#### Outcome measurement

2.1.6

The visual analogue score is done by drawing a straight line on a piece of white paper, with one end representing a score of 0 and 1 end representing a score of 10, and allowing the patient to choose a score based on their subjective feelings. Zero means the patient is not in any pain; below 3, indicates moderate pain; 4 to 6, more significant pain; and 7 to 10, very severe and unbearable pain.^[13]^

The Neck Disability Index score is commonly used in clinical practice to evaluate the functional status of the cervical spine. The scale includes 10 areas of pain, personal care, lifting, reading, headache, concentration, work, driving, sleep and recreation. Each item is scored out of 5, with the total score ranging from 0 (no impairment) to 50 (complete paralysis), the higher the score the greater the dysfunction.^[14]^

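### The non-normal fallback labels a paired-samples test as a between-group comparison (most likely a slip for within-group), and a normality pre-test of unstated form decides when that fallback applies

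*Protocol article*

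**What the plan says.** All of this is in the protocol article, mainly under Statistical analysis.

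- **Pre-test.** A Kolmogorov–Smirnov "test of normality was used for all continuous variables in the 3 groups". To use mean and SD, "the 3 groups had to be normally distributed". Neither the version of the test (with or without the Lilliefors correction for an estimated mean and SD) nor a level specific to it is given; the section states one overall significance level of 0.05.
- **If normal.** MANOVA between groups with SNK post hoc tests; "within-group comparisons were conducted using the" paired t test.
- **If not normal.** "If the data did not conform to a normal distribution, comparisons between groups were made using a nonparametric test for paired samples", and then, in the same sentence, "comparisons between groups were made using a nonparametric test for multiple samples".
- **Pain score (Outcome measurement).** A line from 0 to 10, "allowing the patient to choose a score based on their subjective feelings". The resolution at which the score is recorded is not stated.
- **Sample size calculation.** "Effect size = 0.30, α=0.05, power = 0.92, group size 3 and number of repeated measures of 2 were selected", giving 81, then 90 after allowing for attrition, 30 per arm.

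**The concern.** Two things are wrong with the rule as written.

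First, the fallback sentence gives two incompatible tests for one comparison. Patients are randomised individually 1:1:1 and nothing links a patient in one arm to a patient in another. A paired test between arms would return a P value that depends on the order of rows in the data file. It could not use all patients once the arms differ in size, which is likely because the plan itself allows for 11% attrition. Meanwhile the comparison for which a paired test is right, week 0 against week 4 within an arm, has no fallback.

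Second, the method for each outcome is chosen by a test on that outcome's own data. Pain, disability and the EMG indices could be analysed by different methods in the same report. For the pain score, the choice would turn on details that the article does not fix. Those details can be settled after the data are seen, so the rule does not pin down the efficacy analysis.

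**Working it through.** **1. The plan's own figure.** Noncentral F power for a repeated-measures F-test with f = 0.30, α = 0.05, k = 3 groups and m = 2 measures. The correlation ρ between the two measures is not stated.

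- Between-factors: λ = f²·N·m / [1 + (m−1)ρ], df 2 and N−3.
- Within-between interaction: λ = f²·N·m / (1−ρ), df 2 and N−3.
- With ρ = 0 both give λ = 0.09 × 81 × 2 = 14.58 at N = 81 and power 0.928. At N = 78 the power is 0.918, so 81 is the smallest multiple of 3 that reaches 0.92. The stated 81 is reproduced.
- Attrition: 81 × 1.11 = 89.9, hence 90. (Dividing instead, 81 / 0.89 = 91.0, differs trivially.)

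Neither correcting the wording nor specifying the pre-test enters these formulas, so no stated number changes.

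**2. The two branches side by side.**

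| Comparison | Normal data | Non-normal data, as written | Non-normal data, if the first 'between' is read as 'within' |
|---|---|---|---|
| Between the 3 arms | MANOVA, SNK | paired-samples test and also multiple-sample test | multiple-sample test |
| Within arm, week 0 to 4 | paired t test | none | paired-samples test |

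The last column matches the normal branch row by row. Changing one word removes both the contradiction and the gap.

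**3. How often the pre-test sends the pain score to the fallback.** The article gives no pain mean, SD, shape or resolution, so all of these are assumptions. Normal or gamma values were limited to 0–10 and recorded continuously, to 0.1, to 0.5 or in whole points. There were 40,000 simulated arms of 30 per scenario, tested at 5%. The critical distance is 0.159 with the Lilliefors correction and 0.242 without. If p is the chance that one arm fails, the chance that at least one of three fails at one visit is 1 − (1−p)³.

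Example, mean 5 and SD 2:
- Lilliefors, whole points: 1 − (1 − 0.473)³ = 0.854
- Lilliefors, continuous: 1 − (1 − 0.046)³ = 0.132
- Uncorrected, whole points: 1 − (1 − 0.012)³ = 0.036

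Across scenarios, chance that at least one arm fails at one visit:

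| Pain score | Recorded | Lilliefors | Uncorrected |
|---|---|---|---|
| Roughly symmetric (mean 3–6, SD 1.5–2) | continuous or 0.1 | 13–16% | under 1% |
| | 0.5 | 37–55% | under 1% |
| | whole points | 85–99% | 4–15% |
| Skewed or near the floor (mean about 1–2) | continuous or 0.1 | 48–94% | 0.5–10% |
| | whole points | about 100% | 35–92% |

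The full range is under 1% to about 100%. Only the pain score was simulated; the disability index and the EMG frequencies were not.

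**The case against.** **The sentence supplies the right test.** This stands. The second clause names a multiple-sample test, which suits three independent arms, and the parallel with the normal branch makes 'within' the natural reading of the first clause. A reader who stops at the first clause might infer that the plan's only between-group fallback is a paired test. The document does not support that. An analyst would probably notice the slip, since a paired test cannot be run on all patients in arms of unequal size. It is nevertheless an error in a stated rule and should be corrected.

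**The pre-test may rarely matter.** This stands in part. A reader might infer that a 0–10 pain score will fail the pre-test almost every time. That holds only for whole-point recording with the Lilliefors version, or for some strongly skewed scores. The bands in Outcome measurement (below 3, 4 to 6, 7 to 10) hint at whole points but leave a score of 3 without a band, so they prove nothing. The supportable statement is that the frequency cannot be known from the article.

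**The pre-test is applied to raw values, not residuals.** This criticism would fail. Normality is checked within each group, where residuals from a group-means model are the values minus a constant, so the test gives the same answer on either.

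**No damage is computed, and some detail belongs to an analysis plan.** This is fair. Read as intended, the gate switches between two recognised methods by a rule stated in advance. No type I error inflation or loss of power has been shown. The absence of a post hoc procedure in the fallback is detail that an article may leave to the analysis plan, and it is not part of this point.

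**Conclusion.** The fallback sentence is wrong as written: it gives a paired-samples test for comparing independent arms, contradicts itself in the next clause, and leaves the within-group comparison without a fallback. That follows from the text alone. Reading it as a one-word slip rests on the parallel with the normal branch; this is very likely but not certain.

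The data-driven choice of analysis is a weakness, not a demonstrated bias. Its reach for the pain score, from under 1% to about 100%, rests on the assumed distributions, 30 patients per arm and a 5% pre-test. The width of that range is the finding, since the version of the test and the recording resolution are left open and the skew will be known only from the data.

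Severity is minor to moderate. No sample-size figure is affected by the correction.

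**What to change.** 1. In Statistical analysis, change the first clause of the fallback to within-group comparisons and keep the multiple-sample test for between-group comparisons, stating that it is for independent groups. This costs one or two words.
2. Preferably, drop the normality gate. Pre-specify, for each continuous outcome, one ANCOVA of the week-4 value on group, adjusted for the week-0 value, with a rank-based test as a sensitivity analysis reported whatever the data look like. Both values are already collected (Table 1), so this costs a few sentences and no new data.
3. If the gate is kept, state the version of the Kolmogorov–Smirnov test, its level, the visit or visits at which it is applied, and the resolution at which the pain score is recorded.
4. Leave 81 and 90 as they are, but note in Sample size calculation that they were obtained under the MANOVA F-test. If ANCOVA becomes the main analysis, the stated power of 0.92 should not be presented as its power, because it depends on the model and on a correlation that the article does not give.
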